## Abstract

**Background:**

Musculoskeletal disorders are very common in patients with diabetes mellitus (DM). The upper limb is one of the regions that is most frequently affected generally presenting limited joint mobility, pain, and a decreased muscle strength. Most clinical trials with a focus on shoulder musculoskeletal rehabilitation are carried out in patients who do not present DM. Thus, the purpose of the present study is to compare the effects of two distinct treatment protocols (conventional shoulder musculoskeletal rehabilitation combined with aerobic exercises versus solely conventional shoulder musculoskeletal rehabilitation) on shoulder pain, function, strength, kinematics, and supraspinatus tendon thickness in patients with type 2 DM after 12 weeks of intervention and a subsequent follow-up at week 20.

**Methods:**

A randomized controlled superiority trial will be conducted. Participants with a clinical diagnosis of type 2 DM of both sexes, age between 40 and 70 years, presenting shoulder pain will be randomly assigned to one of the following groups: (1) conventional shoulder musculoskeletal rehabilitation combined with aerobic exercises; (2) solely conventional shoulder musculoskeletal rehabilitation. All individuals will be evaluated before starting the treatment protocol (baseline) and at the end of treatment (post 12 weeks) and as a follow-up at 20 weeks. The shoulder function assessed by the SPADI (Shoulder Pain and Disability Index) questionnaire will be considered as primary outcome; the secondary outcome will be shoulder pain, measured with NPRS scales. Other outcomes will include range of motion, measured using a digital inclinometer; isometric shoulder muscle strength, measured using a manual muscle dynamometer; shoulder kinematics, measured using three-dimensional inertial units measurement; supraspinatus tendon thickness, measured using an ultrasound; AGE accumulation, using a skin autofluorescence measurement; and HbA1c (hemoglobin a1c), fasting glucose and lipid profile measured by a simple blood test.

**Discussion:**

DM is a highly prevalent disease and a public health problem worldwide, and the upper extremity musculoskeletal disorders in DM are barely recognized and largely underestimated. In this way, it would be interesting to analyze if the combination of aerobic exercises with conventional musculoskeletal rehabilitation protocols could generate better results in the functionality, pain, mobility and an improvement in the biochemical aspects related to the hyperglycemia of these patients compared to solely the conventional musculoskeletal rehabilitation.

**Trial registration:**

ClinicalTrials.gov NCT04817514. Registered on March 26, 2021.

## Background and rationale {6a)

Diabetes mellitus (DM) has become a public health problem, since approximately 537 million adults worldwide are living with the disease in 2021, and it is estimated that this number will increase to approximately 784 million adults worldwide in 2045 [1]. Chile ranks as the second country in South America with the highest prevalence of DM, with an estimation of 1,262,200 people, which represents 9.8% of the adult population aged 20–79 years [1].

Besides the most reported complications of DM, such as cardiovascular disorders and peripheral neuropathy, musculoskeletal disorders are also a very common finding in this population [2, 3]. These disorders receive relatively little attention [4, 5]; however, they result in physical and psychological harm in people with DM, compromising their quality of life. Upper limbs are frequently affected in this population, generally presenting limited joint mobility, pain, and decreased muscle strength [2–6]. According to the literature, individuals with DM present 27.5% of prevalence of shoulder complex disorders, such as rotator cuff injuries and adhesive capsulitis, compared to only 5% in the non-diabetic population [5, 6].

The mechanisms of upper extremity musculoskeletal injuries in subjects with DM are still not clear. Some evidence suggests that accumulation of the non-enzymatic advanced glycation end-products (AGEs), due to hyperglycemia, increases the crosslinking in collagen [7]. This increase can generate abnormal collagen deposits in tendons, ligaments, and skin, making connective tissues thicker, rigid, and weaker, leading to a diffuse arthrofibrosis [2, 8–10].

The literature shows that patients with DM and adhesive capsulitis present a greater difficulty in achieving the desired results in their musculoskeletal rehabilitation protocol compared to patients without DM [11–13]. This could be explained by the fact that the mechanisms related to musculoskeletal injuries in patients with DM are different from the general population and that the rehabilitation protocols are usually focused on the symptomatic structure without considering the systemic disease [12, 13]. A wide range of studies have demonstrated that aerobic exercises are the most effective way for glycemic control, reducing cardiovascular risk factors, contributing to weight loss and well-being [14, 15]. Thus, aerobic exercise could be an important complementary strategy in musculoskeletal rehabilitation protocols for patients with DM. In addition, most clinical trials with a focus on shoulder musculoskeletal rehabilitation are carried out on patients who do not present DM or only patients with a specific disorder such as adhesive capsulitis, not considering other shoulder dysfunctions. Research in this area is scarce, perhaps because other diabetes complications have been considered more life-threatening and more important, such as cardiovascular disease. However, musculoskeletal disorders may decrease physical mobility and represent a substantial burden on morbidity and on the quality of life of this population.

Therefore, research is needed to better understand whether the addition of aerobic exercises to a standard shoulder rehabilitation program could help reduce musculoskeletal complications in this population.

## Objectives {7}

The main purpose of this study is to compare the effects of two distinct treatment protocols (conventional shoulder musculoskeletal rehabilitation combined with aerobic exercises versus solely conventional shoulder musculoskeletal rehabilitation) on shoulder function, range of motion (ROM), pain, strength, kinematics, and supraspinatus tendon thickness in patients with type 2 DM after 12 weeks of intervention, and a subsequent followup at the week 20 (8 weeks after the end of the protocol). As a secondary objective, we will evaluate the association between AGE accumulation and shoulder pain, function, strength, kinematics, and supraspinatus tendon thickness in individuals with type 2 DM.

The hypothesis is that the addition of aerobic exercises to the shoulder-specific rehabilitation protocol will promote a greater decrease in shoulder pain and increase in functionality, range of motion, strength, and an adequate shoulder kinematics after 12 weeks, and a follow-up at week 20. Furthermore, regarding the association, the hypothesis is that a higher AGE accumulation is associated with higher shoulder pain, dysfunction, tendon thickness, shoulder kinematic disorders, and lower muscle strength in patients with type 2 DM.

## Trial design {8}

This is a randomized controlled superiority trial, single-blind, two-arm and parallel-group study. Participants will be randomly assigned to one of the following groups: (1) conventional shoulder musculoskeletal rehabilitation combined with aerobic exercises; (2) solely conventional shoulder musculoskeletal rehabilitation.

## Methods: participants, interventions, and outcomes

### Study setting {9}

The study will be performed in the Laboratory of Clinical Research in Kinesiology from the Universidad Católica del Maule – Talca, Chile.

### Eligibility criteria {10}

#### Inclusion criteria

The inclusion criteria will be participants with a clinical diagnosis of type 2 DM (with at least 1 year of diagnosis), of both sexes, between 40 and 70 years old, presenting shoulder pain (unilateral or bilateral) for at least 3 months with a pain intensity score from 3 points on a numerical pain rating scale (NPRS).

#### Exclusion criteria

Participants will be excluded if they present a history of shoulder surgery; recent history of fracture in the upper limb; cognitive deficits that make it difficult to understand verbal commands; neuromuscular diseases; central nervous system diseases; diagnosis of cardiovascular disease; kidney chronic disease and have undergone shoulder rehabilitation within the past 6 months

### Who will take informed consent? {26a}

The MFQ and RIC researchers will be in charge of contacting the participants, inviting them to participate in the study. The researchers will explain the objectives of the study and ethical implications, followed by evaluation according to the eligibility criteria. If the participant is eligible and accepts to participate in the study, the informed consent will be signed in 2 copies: one for the participants, and one for the researcher.

### Additional consent provisions for collection and use of participant data and biological specimens {26b}

This is not applicable, since this study does not involve any biological specimens.

## Interventions

### Explanation for the choice of comparators {6b}

Considering that the majority of the protocols for shoulder rehabilitation only focus on the musculoskeletal disorder, without considering the presence of metabolic diseases, the rehabilitation protocols to be compared are the following: (1) a protocol only focused on shoulder rehabilitation (shoulder-specific rehabilitation protocol); (2) a protocol of shoulder rehabilitation associated to an aerobic exercise, with an emphasis in the metabolic disease (shoulder-specific rehabilitation combined with aerobic exercises protocol).

### Intervention description {11a}

Participants who meet the inclusion criteria for this study will initially be evaluated for demographic data including age, sex, weight, height, occupation, and time since type 2 DM diagnosis. The order of assessment of the main outcomes will be randomized. After participants complete the outcomes assessment, they will be randomly assigned to one of the two treatment groups: (1) shoulder-specific rehabilitation protocol group (SRG); or (2) shoulder-specific rehabilitation protocol plus aerobic exercise group (SAG). The randomization sequence will be performed through a computerized algorithm in GraphPad.

All measurements will be performed on the symptomatic side for shoulder pain. In the case of bilateral pain, the side with greater severity will be considered in the study as proposed in previous studies [16]. However, treatment will be carried out bilaterally. Outcomes measures will be performed always by the same evaluator.

Both treatment protocols will last 12 weeks, and they will be performed twice a week. All individuals will be evaluated before starting the treatment protocol (baseline), at the end of treatment (post 12 weeks), and at week 20 (8-week follow-up after the intervention) (Fig. 1). To minimize bias, the evaluator responsible to measure the main outcomes will be blinded to the type of treatment being performed. Before, during, and after each session, blood pressure, heart rate, and rating of perceived exertion will be measured.

**Fig. 1 Fig1:**
[figure not shown]
The recommended SPIRIT figure with the participant timeline

#### SRG: shoulder-specific rehabilitation group

The SRG protocol will be performed on groups with a maximum of 5 participants. Exercise intensity and difficulty will progress after completing 4 weeks of treatment, by increasing range of motion and loads (dumbbells) or resistance (elastic bands) in the exercises that are convenient. Each session will consist of 6 exercises: (1) pendulum exercise (10 repetitions—maintenance for 20 s); (2) slide in flexion of the arms on the table (2 sets of 10 repetitions, maintenance in maximum range for 20 s); (3) abduction and adduction mobility (2 sets of 10 repetitions, maintenance for 20 s) and full can abduction exercise; (4) wall slide—sliding of the arms on the wall (2 series of 10 repetitions, maintenance of 20 s); (5) internal and external rotation mobility (2 sets of 10 repetitions, maintenance for 20 s) and external rotators strengthening; (6) stretching of the posterior capsule (cross-body) and stretching of pectoralis minor (3 repetitions of 30 s, each). Pain will be evaluated during the protocol using the NPRS scale. The exercises proposed in this protocol are those already demonstrated to improve function, strength, range of motion, and pain in musculoskeletal disorders of the shoulder complex for general population [17, 18].

Each session of this protocol will last between 30 and 35 min. All sessions will be supervised by a physiotherapist with experience in physical exercise.

#### SAG: shoulder-specific rehabilitation combined with aerobic exercises group

The SAG will perform the shoulder rehabilitation protocol presented above combined with an aerobic exercise program. The aerobic program will last 20 min per session at 40% of the reserve heart rate (HRR), progressing up to 40 min with a maximum of 60% of the HRR in the last 2 weeks (weeks 11 and 12), according to the recommendations for patients with type 2 DM proposed by the American College of Sports Medicine [19]. The program will be carried out in groups of 5 participants and each session will consist of 3 stages: (1) warm-up (5 min): patients will perform stretches of the main muscle groups; (2) aerobic exercise on a treadmill with continuous heart rate monitors (Polar Electro Oy, Kempele, Finland), which will be used to adjust workload to achieve the target heart rate (15–40 min); (3) cooldown (5 min): stretching of the main muscle groups which were worked during the sessions and relaxation. In this way, the rehabilitation protocol of SAR group will last a total of approximately 90 min maximum. During sessions, heart rate will be monitored by a heart rate monitor (Polar Vantage, Finland), and rating of perceived exertion will be measured using the Borg CR20 scale, which should remain approximately between 11 and 13 [19]. All sessions will be supervised by a physiotherapist with experience in physical exercise.

### Criteria for discontinuing or modifying allocated interventions {11b}

Participants will be informed that exercises and rehabilitation interventions, other than those that will be received during the duration of the study, will not be allowed. Participants with less than 80% treatment attendance will be excluded from the study. Furthermore, data such as blood pressure, heart rate, saturation, and rating of perceived exertion will be measured before, after, and during the rehabilitation sessions. Capillary blood glucose will be evaluated at the beginning and at the end of each session. If the patient presents signs or symptoms of decompensation such as glycemia> 200 mg/dl or <80 mg/dl, systolic blood pressure > 180 mmHg, or diastolic blood pressure > 100 mmHg at rest, the session or evaluation will be immediately suspended, and the necessary measures will be taken.

### Strategies to improve adherence to interventions {11c}

The researchers will ask for feedback from the patients throughout the sessions, to know if there is anything that could be improved, and about the patient’s satisfaction. If they notice anything that could help to improve their adherence, it will be added, without changing the intervention protocol. Furthermore, the patients will be reminded weekly about their rehabilitation sessions through messaging.

### Relevant concomitant care permitted or prohibited during the trial {11d}

Participants will be instructed to keep their pharmacological treatment during the entire study and inform researchers of any changes in their medications. Participants will be informed that exercises and rehabilitation interventions, other than those that will be received during the duration of the study, will not be allowed.

### Provisions for post-trial care {30}

At the end of the study, if SAG protocol is effective in promoting higher improvement than the SRG protocol, the same treatment will be offered to SRG participants at no cost**.**

### Outcomes {12}

The results will be evaluated at 3 points: (1) baseline (before starting the intervention program), (2) after 12 weeks of intervention (after 48 h to 1 week from the last intervention), and (3) at the week 20 (follow-up). Regarding the outcomes, the shoulder assessed by the SPADI (Shoulder Pain and Disability Index) questionnaire will be considered as primary outcome; the secondary outcome will be shoulder pain, measured with NPRS scales. Other outcomes will include range of motion, measured using a digital inclinometer; isometric shoulder muscle strength, measured using a manual muscle dynamometer; shoulder kinematics, measured using three-dimensional inertial units measurement; supraspinatus tendon thickness, measured using an ultrasound; AGE accumulation, using a skin autofluorescence measurement; and HbA1c (hemoglobin a1c), fasting glucose and lipid profile measured by a simple blood test.

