#### HbA1c (hemoglobin a1c), fasting glucose and lipid profile

HbA1c, fasting glucose, and lipid profile will be evaluated through blood tests that will be performed in a clinical laboratory, at the beginning (before starting the treatment protocol), after the 12-week intervention (3–7 days after the last session).

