### Methods in analysis to handle protocol non-adherence and any statistical methods to handle missing data {20c}

The study will include only participants who attended at least 80% of the sessions and performed all the assessments (per-protocol). Furthermore, missing data will be handled by intention-to-treat analysis using the multiple imputation method.

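### The post-treatment visit window is counted from an undefined last session, and no visit is provided for participants who stop, so some primary outcomes may be mistimed or imputed when they could be observed

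*Protocol article*

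**What the plan says.** All references are to the protocol article.

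- **Post-treatment visit.** Outcomes {12} sets it "after 12 weeks of intervention (after 48 h to 1 week from the last intervention". Intervention description {11a} places the two later assessments "at the end of treatment (post 12 weeks), and at week 20 (8-week follow-up after the intervention".
- **Blood tests.** The section on HbA1c, fasting glucose and lipids places them "after the 12-week intervention (3–7 days after the last session".
- **Programme.** Intervention description {11a}: "Both treatment protocols will last 12 weeks, and they will be performed twice a week".
- **Follow-up.** Objectives {7} describes a "followup at the week 20 (8 weeks after the end of the protocol".
- **Low attendance.** Section {11b}: "Participants with less than 80% treatment attendance will be excluded from the study". Section {20c} likewise restricts the study to those with at least 80% of sessions and all assessments.
- **Missing data.** The same section {20c} adds that "missing data will be handled by intention-to-treat analysis using the multiple imputation method".

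The text gives no window in days from randomisation or programme start, does not define the last intervention as scheduled or attended, and gives no visit rule for a participant who stops. The participant timeline in Fig. 1 is not visible to this review.

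**The concern.** The only limits in days run from an event that, on one reading, depends on what the participant does after randomisation. If the last attended session is meant, the date of the primary-outcome visit moves with attendance. The two conditions in Outcomes {12}, 12 weeks completed and at most 1 week since the last session, then cannot both be met by someone who leaves well before the end. Site staff would have to measure early or record no valid visit.

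At stake is whether SPADI is observed at a comparable time in both arms. An intention-to-treat comparison needs a week-12 value for everyone randomised. A value that was obtainable but never scheduled becomes a missing value to be imputed, and a visit not made cannot be recovered at the analysis stage. With 20 participants per arm, a few such values count. Attendance could also differ by arm, since combined sessions run to about 90 minutes against 30 to 35 minutes for shoulder rehabilitation alone. That is a plausible risk, not something the protocol documents.

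**Working it through.** The plan states no figure for visit timing that could be reproduced, so the check sets the timing conditions against each other.

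**Inputs.** 12 weeks at two sessions a week ({11a}); 80% attendance ({11b}, {20c}); window of 2 to 7 days after the last session (Outcomes {12}); 3 to 7 days for blood tests. Assumption: the last scheduled session falls at the end of week 12 (day 84).

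**Permitted absence.** 12 × 2 = 24 sessions. 0.8 × 24 = 19.2, so at least 20 must be attended and 4 may be missed. At two a week that is 4 / 2 = 2 weeks.

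**Window, week = (day of last session + 2 to 7) / 7.**

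| Last session attended | Visit window | Blood-test window |
|---|---|---|
| End of week 12 (day 84) | 86/7 to 91/7 = week 12.3 to 13.0 | 87/7 to 91/7 = week 12.4 to 13.0 |
| End of week 10 (day 70, final four missed) | 72/7 to 77/7 = week 10.3 to 11.0 | 73/7 to 77/7 = week 10.4 to 11.0 |

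The largest shift for a participant who still meets the attendance rule is 2 weeks.

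**When both conditions can hold.** The visit must be no earlier than day 84 and no later than the last session plus 7 days, so the last session must fall on day 84 − 7 = 77 or later. Anyone whose last attended session is before about the end of week 11 has no date that meets both.

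**Stopping before session 20.** 19/24 = 79.2%, below 80%. Such a participant is excluded by {11b} and {20c} whatever the visit window.

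**Illustration of size for retained participants.** Assumptions not in the protocol: the between-group difference builds linearly over 12 weeks, and a fraction f is measured 2 weeks early. No SD is stated; 16 per group with 80% power in a two-sided 5% t test implies d = 1.02 for the 16.8-point difference, that is, an SD of about 16.4. The difference becomes 16.8 × (1 − f × 2/12), and power is recalculated at 16 per group.

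| f | Difference (points) | Power |
|---|---|---|
| 0 | 16.8 | 80% |
| 10% | 16.5 | 79% |
| 20% | 16.2 | 77% |
| 30% | 16.0 | 76% |

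**How many might stop.** The sample-size section raises 16 to 20 per group for withdrawals: 16 / (1 − 0.2) = 20, an allowance of 4 per arm.

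**The case against.** The strongest reply is that the text already fixes a nominal week-12 visit. Outcomes {12} requires 12 weeks of intervention as well as the short gap, the abstract and {11a} both place the visit after 12 weeks, and the programme has a fixed length. The 48-hour minimum fits the adverse-event section, which says exercise-related soreness tends to last about that long. No sentence mentions the last attended session. An article may also leave visit windows to a fuller protocol, and the timeline figure is not shown here. This stands to a large extent: for anyone who attends to the end there is no conflict, and a missing window alone would be minor. What remains is that the anchor actually stated is ambiguous in exactly the cases where it matters.

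Three stronger readings are tempting, and the document does not support them.

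- A reader might infer that someone who stops in week 6 is assessed in week 6 or 7 under the week-12 label. That visit would breach the 12-week condition in the same sentence, and the participant is excluded by the attendance rule in any case. The loss of stoppers comes mainly from {11b} and {20c}, not from the visit window.
- A reader might see two competing anchors for follow-up in "at week 20 (8-week follow-up after the intervention". Objectives {7} counts from the end of the protocol, and 12 + 8 = 20, so the two descriptions agree for a fixed 12-week programme.
- A reader might credit the change with the power of 20 instead of 16 observed participants per arm. That would be the value of having no loss to follow-up at all. Nothing shows that a new anchor would recover every withdrawal.

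**Conclusion.** The point holds in a limited form. The post-treatment window is tied to a last session that is not defined as scheduled or attended. If it means attended, a participant who satisfies the attendance rule can be measured up to 2 weeks early or fall outside the window. Under the linear-build assumption, power at 16 per group falls from 80% to between 76% and 79% when 10% to 30% are affected, so the effect on retained participants is probably small.

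The larger consequence concerns those who stop. With the exclusion rule in force the document provides no assessment for them, yet it announces an intention-to-treat analysis with multiple imputation. Their outcomes would be imputed although some could be observed. The benefit of a change is outcomes that are observed and comparably timed; it should not be argued as a gain in power. The change is worth making because it is cheap and cannot be made after the visits are missed.

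**What to change.** Date both visits from randomisation, or from the first scheduled session, for every randomised participant whatever their attendance:

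- the post-treatment visit in, for example, week 12 to 13, and at least 48 hours after any session just attended;
- the follow-up visit at week 20, with a stated window;
- the blood tests on the same footing as the post-treatment visit.

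Invite participants who stop to both visits, with SPADI and NPRS as the minimum. Reconcile this with {11b} and {20c}, so that low attendance ends neither outcome collection nor membership of the intention-to-treat set. A per-protocol analysis can still be reported alongside.

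The cost is about one sentence on timing, a matching edit to the exclusion wording, and a few invitations, about 4 per arm on the protocol's own withdrawal allowance. No procedure is added. Some of those invited will decline, so imputation will still be needed, but for fewer participants.
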